# Effectiveness and safety of Bushen Huoxue granules in treatment of premature ovarian insufficiency: study protocol for a randomized, double-blinded, placebo-controlled, and multicenter clinical trial

**DOI:** 10.1186/s13063-021-05838-w

**Published:** 2021-12-04

**Keywords:** Chinese herbal medicine, Premature ovarian insufficiency, Bushen Huoxue, Clinical trial protocol

## Abstract

**Introduction:**

Premature ovarian insufficiency (POI) seriously affects the quality of life, endocrine function, and fertility of women of childbearing age. Currently, hormone replacement therapy for POI has some limitations, either with low efficacies or high side effects. Bushen Huoxue (BSHX) plays an important role in alleviating clinical symptoms and improving health status of POI patients. This placebo-controlled, randomized, double-blind, and multicenter clinical trial protocol aims to evaluate the effectiveness and safety of BSHX in women with POI.

**Methods and design:**

We plan to recruit 150 women with POI from four participating hospitals in China. Participants will be randomized in a 1:1 to receive oral BSHX or BSHX placebo. All participants will be treated for 3 months and will be followed up for another 3 month. The primary outcome is questionnaire scores based on the changes in the total symptoms, which is the Chinese version of the Menopause-Specific Quality of Life (CMS) (Nie G, Yang H, Liu J, Zhao C, Wang X, Menopause 24(5):546–554, 2017). CMS will be measured before the intervention, at 3 months and 6 months after randomization for all participants. The other measurements include serum sex hormone levels, anti-Müllerian hormone (AMH) levels, ovarian peak systolic velocity (PSV; cm/s), and antral follicle count (AFC). In this study, the regulatory effects of traditional Chinese medicine on hormones were evaluated by the changes of serum sex hormone levels, which include serum estradiol (E2), luteinizing hormone (LH), and follicle-stimulating hormone (FSH). These indicators will be measured before intervention and at 3 months after randomization.

**Ethics and dissemination:**

This study was approved by the Research Ethics Committee of Jiangsu Province Hospital on Integration of Chinese and Western Medicine (2019LWKY014). All participants will provide written informed consent prior to randomization. The results of this research will be presented to academic conferences and peer-reviewed journals.

**Trial registration:**

ChiCTR1900028451. Registered on 22 December 2019, https://www.chictr.org.cn/index.aspx.

**Supplementary Information:**

The online version contains supplementary material available at 10.1186/s13063-021-05838-w.

## Strengths and limitations of this study

►The results from this multicenter, randomized, double-blinded, placebo-controlled clinical trial will provide new evidence of the efficacy of Bushen Huoxue for premature ovarian insufficiency.

►This is a well-designed study to assess the efficacy and safety of Bushen Huoxue for the treatment Premature Ovarian Insufficiency.

► We use effective and non-invasive methods Chinese version menopause-specific Quality of Life questionnaire to detect the efficacy of drugs, which is easy for investigators to operate and more acceptable to participants.

► Larger-scale clinical studies of Bushen Huoxue among more diverse populations are needed to further confirm these findings.

## Introduction

POI is a clinical syndrome in which ovarian activity declines in women before the age of 40. It is characterized by menstrual disorders (such as menopause, rare menstruation) and accompanied by high gonadotropin and low estrogen, which seriously affects the reproductive health and quality of life of women of childbearing age [1]. In recent years, with the increasing fierce social competition and the change of working style, the incidence of POI among women under 35 years old is about 4%, and it is increasing year by year and showing a younger trend [2]. In addition, there are many causes of iatrogenic POI [3].

The etiology and pathological mechanism of the disease are not yet available, so modern medicine has no effective method to restore ovarian function. The most commonly used treatment is hormone supplementation until the average age of natural menopause in people with no contraindications. Some women need this therapy for decades. But, In 2017, the United States Preventive Services Task Force reviewed the evidence that did not address hormone therapy for preventing or treating menopausal symptoms [4]. In previous clinical studies, the results showed that estrogen replacement therapy did not increase pregnancy rates or follicle formation in SPOI women [5, 6] and had no positive effect on the long-term management of bone mineral density in women with SPOI [7]. More than that, the risk of developing tumors is increased if progesterone and estrogen are used in combination [8]. Furthermore, women who take oral estrogen than transdermal estrogen have an increased relative risk of stroke [9]. If women have a history of breast or ovarian cancer, hormone therapy should be replaced [10, 11].

To solve the current problems in POI treatment, our goal is to search for an effective therapy for POI with fewer side effects. In China, traditional Chinese medicine (TCM) therapy has been widely used to treat POI for thousands of years. According to TCM theory, the basis of female physiology is blood, and her reproductive capacity is dominated by kidney gas. Kidney deficiency and blood stasis are the basic pathogenesis of POI [12]. BSHX is a mixed herbal formula that has been used to treat POI by systematically balancing the body’s Yin and Yang, and correcting the pathophysiological condition of kidney deficiency and blood stasis. Therefore, the BSHX plays a role in the treatment of POI. It is a compound medicine consisting of ten different Chinese herbals (Table S1 in supplementary materials).

Previous clinical studies have shown that BSHX can improve patients’ quality of life by alleviating symptoms, such as lower abdominal pain, hot sweat, lower back, and weak knees. At the same time, BSHX can effectively regulate the level of serum FSH and E2 and improve ovarian function. Therefore, it is worth popularizing and using in clinic [13]. Related animal experiments have proved that BSHX has obvious therapeutic effect on POI mice, which may be through immune protection, reducing the infiltration and damage of ovarian inflammatory cells [14]. Moreover, pharmacological studies have demonstrated that BSHX can interfere with POI through many aspects, which can not only regulate reproductive endocrine hormones, but also prevent premature apoptosis of follicles, improve pelvic blood microcirculation, increase ovarian volume and cavity follicle count, and regulate related signal transduction pathways. Li et al. reviewed the literature on randomized controlled clinical trials of BSHX in the treatment of POI. A meta-analysis of clinical total effective rate, symptom score, menstrual recovery rate, and improvement of serum sex hormones was conducted. The results showed that BSHX appears to be a safe and effective drug to treat patients with POI, and herbal may be superior to western medicines [17]. Studies initially reveal that BSHX interferes with POI through multiple targets. The comprehensive network effect of points, multiple links, and multiple mechanisms have achieved certain research results [15]. However, the study did not include a placebo control group, and there have been few clinical trials with strictly relevant designs. Therefore, in this study, the aim is to conduct a double-blind, randomized, placebo-controlled, multicenter trial of women with POI in China. The primary objective is to evaluate the effectiveness and safety of BSHX treatment for women with POI.

## Methods

### Study design and participants

This is a randomized, double-blinded, placebo-controlled, four-center clinical trial protocol for studying the effects of BSHX on women with POI. There are four hospitals (Table S2 in supplementary materials) that have participated in this project. The clinical trials were conducted according to the principles of the World Medical Association Declaration of Helsinki and the guidelines of Good Clinical Practice of the International Conference on Harmonisation (ICH-GCP). The trial was registered as ChiCTR1900028451 at the Chinese Clinical Trial Registry (https://www.chictr.org.cn/index.aspx) on 22 December 2019. This study has been approved by each hospital’s ethics committee and the responsible regulatory authorities. All participants will provide written informed consent before randomization. Qualification screening and information on demographic and clinical characteristics will also be collected. After passing the qualification screening, participants will undergo a number of medical examination to obtain baseline data. These data are the minimum eligibility criteria for each participant. Meanwhile, it is possible to screen out respondents who may not follow the research procedures. All study participants will be randomly divided into two parallel groups, the BSHX group, and the placebo group, respectively. The trial consisted of 3 months of treatment, interviews at 2-week intervals, and 3 months of follow-up, interviews at 4-week intervals. Based on previous clinical trial studies, we will use a 3-month drug observation period to monitor the safety and efficacy of the treatment [16, 18–20]. The study design flow chart is shown in Fig. S1 (in supplementary materials).

### Sample size calculation

Sample size estimation refers to the calculation of the required sample size in order to meet the accuracy and reliability of statistics (the control of type I errors and the guarantee of inspection efficiency) [21]. The sample size of this study was based on the relevant literature reviews and the validity of hypotheses. The main indicator of this study is to detect the difference of the total score (CMS) between the two groups before and after treatment. There is one randomized clinical trial for BSHX in the treatment of POI [13]. However, there is no placebo control group in the clinical trial and the primary outcome measurements were different. Thus, the parameters are not suitable to estimate the sample size of the trial. We referred to other clinical trials of traditional Chinese medicine in the treatment of POI patients [22]. We assumed that BSHX administration would reduce CMS score by 2.9 points and the SD is 7.42 in the study [23]. If a type I error rate of *α* = 0.05, a power of 90 % (type II error rate of *β* = 0.1), then u1 − *α* =1.64, u1 − *β* =1.28. n1 = n2 ≈ 70. During the 3-month treatment period, taking into account the possible protocol violations, and the maximum possible drop-out rate of 15%, we need 148 participants in total to achieve the number of people required for the efficacy analysis. One hundred fifty participants will be recruited for this study, and the following formula was used to estimate the sample size:
$$ n=2\times {\left[\frac{\left({z}_{1-\raisebox{1ex}{$\partial $}\!\left/ \!\raisebox{-1ex}{$2$}\right.}+{z}_{1-\beta}\right)\sigma }{\delta}\right]}^2 $$

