### Randomization and blinding

The randomization sequence is generated by a computer and randomization numbers are hidden in sealed, opaque, and sequentially numbered envelopes, which are properly kept until the end of the trial. Participants will be randomly assigned (1:1) using a computer-generated randomization sequence to receive oral BSHX or BSHX placebo. The statistician who is not involved in recruiting will prepare the randomization list, and the list will not be available to anyone in any center. Researchers who do not participate in the recruitment label the envelopes. Meanwhile the size, color, taste, and shape of the placebo are consistent with the corresponding drugs, and all study groups assigned by different numbers will use the same packages of medicines. All the documents related to the randomization and allocation sequence generation will be kept in a box in a locked cabinet away from the clinical environments. Packages of BSHX and placebo were provided to randomly assigned two groups of women in each hospital’s centers. This is a double-blind trial, in which all researchers and subjects will be blinded for the treatment allocation until the trial is completed. If there is a serious adverse event or an emergency unblinding event, the blind will be immediately broken.

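### The 2.9-point sizing effect is not defined against placebo, and the planned 150 women do not give the stated 90% power whichever way it is read

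*Protocol article*

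**What the plan says.** The Introduction sets the aim: "the aim is to conduct a double-blind, randomized, placebo-controlled, multicenter trial of women with POI in China". Randomization and blinding confirms two arms: "Participants will be randomly assigned (1:1) using a computer-generated randomization sequence to receive oral BSHX or BSHX placebo". The Sample size calculation section names the target as being to "detect the difference of the total score (CMS) between the two groups before and after treatment".

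That section sets aside an earlier randomized trial of BSHX for two reasons: "However, there is no placebo control group in the clinical trial and the primary outcome measurements were different". It then turns to other sources: "We referred to other clinical trials of traditional Chinese medicine in the treatment of POI patients [22". The effect and SD follow in one sentence: "We assumed that BSHX administration would reduce CMS score by 2.9 points and the SD is 7.42 in the study [23".

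The remaining inputs are a type I error of 0.05, power of 90%, normal quantiles of 1.64 and 1.28, about 70 women per arm, a drop-out rate of up to 15%, 148 women needed and 150 to be recruited. The printed formula is the two-sample one, with a factor of 2 and the two-sided quantile. Its delta and sigma are not defined in words.

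The Statistical analysis section compares the arms at month 3 with an independent t-test and also plans paired t-tests within each arm.

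**The concern.** In a two-arm formula, delta has to be the difference between the arms. The only effect given is worded as what BSHX does to the score. Nothing says that it is net of placebo, and no placebo change is stated that would allow a difference to be formed. The section rejects the earlier BSHX trial partly because it lacked a placebo group, yet does not state the replacement effect against placebo either.

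This matters because the primary outcome is a questionnaire that the women complete themselves, so some improvement on placebo is plausible. If 2.9 is BSHX's own change, any placebo improvement comes off it. Correcting the formula's arithmetic alone would then still not secure 90% power. If 2.9 is already net of placebo, the arithmetic alone decides the matter. A reader cannot tell which case applies, and a power of 90% is stated regardless.

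**Working it through.** **Inputs (Sample size calculation).** Delta 2.9; SD 7.42; alpha 0.05; power 90%; about 70 per arm; 15% drop-out; 150 recruited, so 75 per arm at 1:1.

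**1. The plan's own figure.** The printed formula is n = 2 × [(z_alpha + z_beta) × SD / delta]².

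- Two-sided, as printed: 2 × [(1.96 + 1.28) × 7.42 / 2.9]² = 2 × 68.7 = 137.4, so **138 per arm**.
- With the printed quantiles: 2 × [(1.64 + 1.28) × 7.42 / 2.9]² = 2 × 55.8 = 111.6, so 112 per arm.
- Neither gives 70. Omitting the factor 2 gives 68.7 with 1.96 and 55.8 with the printed 1.64.

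**2. Drop-out.** 140 / 0.85 = 164.7, so 165 women, not 148. From 150 women, 15% loss leaves 127.5, about 63.75 per arm.

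**3. Power if 2.9 is already BSHX minus placebo.** The standard error is 7.42 × √(2/n). Power is from the noncentral t distribution, two-sided 5%.

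| Women analysed per arm | SE | 2.9 / SE | Power |
|---|---|---|---|
| 75 (no loss) | 1.212 | 2.39 | 66% |
| 70 | 1.254 | 2.31 | 63% |
| 63.75 (15% loss) | 1.314 | 2.21 | 59% |
| 138 | 0.893 | 3.25 | 90% |

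A one-sided 5% test, to match the printed 1.64, gives about 77% at 75 per arm and 71% at 63.75 (normal approximation). That is also short of 90%.

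**4. Power if 2.9 is BSHX's own change.** The document gives no placebo change, so the first column is an assumption. Net delta = 2.9 × (1 − fraction); SD 7.42, two-sided 5%, no loss.

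| Placebo improvement, share of 2.9 | Net delta | Power, 75 per arm | Power, 138 per arm |
|---|---|---|---|
| 0% | 2.90 | 66% | 90% |
| 10% | 2.61 | 57% | 83% |
| 20% | 2.32 | 48% | 74% |
| 30% | 2.03 | 38% | 62% |
| 50% | 1.45 | 22% | 37% |

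On this reading, a placebo improvement of 0.29 points costs 9 percentage points of power at 75 per arm and 7 at 138.

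**5. What the SD would have to be.** For 90% power at 70 per arm, two-sided, with delta 2.9: SD = 2.9 / [√(2/70) × (1.96 + 1.28)] = 5.3, against the stated 7.42.

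**The case against.** The best defence is that 2.9 was meant as the net difference all along. The section names the between-group difference as its target, prints a two-sample formula and gives 2.9 as the only effect to put into it. In a placebo-controlled trial, saying that a drug would lower a score by some amount can mean relative to control. Rejecting the earlier trial for lacking a placebo arm suggests that its authors knew a placebo-relative figure was needed. Whether the figure they took is placebo-relative depends on cited studies that are not available here. All of this stands, and it is why the wording can be called undefined but not wrong.

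A reader might go further and infer that 2.9 is a before-after change with zero change assumed on placebo, pointing out that about 70 is the size of a single-arm paired test (68.7). The document does not support that as fact. The match needs 1.96 where the section prints 1.64, which would give 56. Dropping the factor 2 from the two-sample formula produces the same 68.7 and says nothing about what 2.9 means.

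It is also fair that the table in step 4 is hypothetical, and that the shortfall in its 0% row is purely an arithmetic error. The Statistical analysis section plans covariance analysis for baseline, which could lower the effective SD if 7.42 is the SD of a score at one time. The sizing section claims no such gain and gives no correlation from which to compute one.

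**Conclusion.** The point holds as a defect of definition together with a power figure that the plan's own inputs do not deliver. The effect is not identified as within-arm or between-arm, no placebo change is stated, and the type of SD is not given.

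On the most favourable reading, with 2.9 net of placebo, 150 women give about 66% two-sided power with everyone analysed and about 59% if 15% are lost, against a stated 90%. This takes 7.42 as the SD that applies to the between-arm comparison. On the less favourable reading power is lower still, and the document does not fix by how much. The 57% to 22% range at 75 per arm rests entirely on assumed placebo improvements of 10% to 50% of 2.9. That 2.9 is a before-after figure, or that placebo was assumed not to change, should not be reported as a finding.

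**What to change.** In the Sample size calculation section:

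- Define delta as the assumed BSHX-minus-placebo difference in mean CMS change at month 3, with its source. If 2.9 already is that difference, say so and keep it.
- If 2.9 is BSHX's own change, state the assumed placebo change as well, and add a short table of power over a range of placebo improvements.
- State whether 7.42 is the SD of the score at one time or of the change, and use the SD that matches the planned comparison.
- Delete the 90% figure and restate the power of the planned 150 women at the defined delta, with and without 15% loss.

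The cost is one rewritten paragraph, possibly a small table, and a less favourable stated power. No added enrolment is proposed, and nothing changes for participants, treatment or visits.

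### The total of 148 does not absorb the stated 15% drop-out: keeping 140 evaluable takes 165, and recruiting 150 leaves about 127

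*Protocol article*

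**What the plan says.** All the figures are in the protocol article, Methods, Sample size calculation:

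- Effect and spread: "We assumed that BSHX administration would reduce CMS score by 2.9 points and the SD is 7.42 in the study".
- Error rates: alpha 0.05 and "a power of 90 % (type II error rate of" 0.1).
- Result: about 70 in each of two groups, hence 140.
- Allowance and resulting total, where violations of the protocol are mentioned as well: "the maximum possible drop-out rate of 15%, we need 148 participants in total to achieve the number of people required for the efficacy analysis".
- Recruitment: "One hundred fifty participants will be recruited for this study". The abstract repeats this target: "We plan to recruit 150 women with POI from four participating hospitals in China".

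Allocation is equal (Randomization and blinding: "Participants will be randomly assigned (1:1) using a computer-generated randomization sequence"). No other section gives a different drop-out rate or a different evaluable number.

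**The concern.** The sentence makes a checkable promise: with 148 women enrolled and the worst expected drop-out, enough remain for the efficacy analysis. The step from 140 to 148 adds only eight women, whereas 15% of 148 is about 22. So the promise looked false on the section's own numbers.

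At stake is what a reader may assume about the finished trial. If the result on the symptom score is null, the reader will look at this section to judge whether the trial could have found an effect. The section says the required number is protected against 15% loss, and it is not. The recruitment target of 150 carries the same shortfall.

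**Working it through.** **Inputs** (Sample size calculation; allocation from Randomization and blinding): 70 per group, 140 in total; loss d = 15%; stated total 148; recruited 150; difference 2.9; SD 7.42; alpha 0.05; 1:1 allocation.

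**1. Trying to reproduce 148.** The usual inflation is N/(1 − d); a cruder variant is N × (1 + d).

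| Method | From 140 in total | From 70 per arm, doubled |
|---|---|---|
| N/(1 − 0.15) | 164.7, so 165 | 83 × 2 = 166 |
| N × 1.15 | 161 | 81 × 2 = 162 |

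Neither gives 148 or 150. Rounding in the 70 does not explain it: 69 per arm gives 138/0.85 = 162.4.

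**2. Loss that the stated totals can absorb.**

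- 148: 1 − 140/148 = 5.4%
- 150: 1 − 140/150 = 6.7%

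**3. Evaluable number at the stated 15%.**

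- 148 × 0.85 = 125.8, which is 14.2 below 140
- 150 × 0.85 = 127.5 (63.75 per arm), which is 12.5 below 140

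**4. Working backwards.** A total of 148 fits a base of about 126 (126/0.85 = 148.2, 63 per arm). With the cruder method it fits 64 per arm (64 × 1.15 = 73.6, so 74, doubled 148). Neither 63 nor 64 appears in the article.

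**5. Effect on power.** Two-sample t-test, noncentral t, difference 2.9, SD 7.42, alpha 0.05. Both sidedness options are shown because the section quotes the one-sided quantile 1.64 but prints a formula with the two-sided one.

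| Per arm | Two-sided | One-sided |
|---|---|---|
| 70 | 63.2% | 74.4% |
| 63.75 | 59.1% | 70.9% |

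The normal approximation gives slightly higher values: 63.8% and 59.7% two-sided, 74.8% and 71.3% one-sided.

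**6. Detectable difference with 90% power at 63.75 per arm** (normal approximation). The standard error is 7.42 × √(2/63.75) = 1.314.

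- Two-sided: (1.96 + 1.28) × 1.314 = 4.26 points
- One-sided: (1.64 + 1.28) × 1.314 = 3.84 points

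The plan assumes 2.9.

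**7. The separate base error.** The printed formula, 2 × [(z + z)σ/δ]², gives 138 per arm two-sided and 113 one-sided (112 with the rounded quantiles 1.64 and 1.28). A figure near 70 appears only two-sided with the factor 2 left out (68.8, so 69). After 15% loss, 138 per arm becomes 163 per arm (326 in total), and 113 becomes 133 per arm (266 in total). The 165 in step 1 therefore repairs only the drop-out step.

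**The case against.** The strongest reply is that drop-outs may not leave the main analysis. The section on removal and dropout says a drop-out's last recorded data are analysed, and the Statistical analysis section makes intention-to-treat in the full analysis set the main approach. On that reading up to 150 women could be analysed, and 127 is closer to a per-protocol count. This stands as a condition on the consequence: the main analysis falls short only to the extent that drop-outs are excluded or contribute less information than complete data. It does not rescue the figure. The sample size section itself makes the allowance in order to secure the number needed for efficacy. If nobody were lost to the analysis, no allowance would be needed and the total would be 140. Neither reading yields 148.

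A second reply is that 70 may be the misprint and 148 the intended total, since 148 fits 63 or 64 per arm. The article does not settle this, and 165 is the right total only if 70 is accepted. But the stated inputs do not produce 63 or 64 from the printed formula either, so 70, 15% and 148 remain mutually inconsistent.

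Third, the error by itself costs about four points of power, and the larger shortfall comes from the base of 70. That is true, and it limits the size of this point. Calling 15% a maximum does not help, because the text says 148 is enough with that maximum taken into account.

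**Conclusion.** The point holds. From the article's own 140 evaluable and 15% loss, the total should be 165 (166 with equal arms), not 148. Recruiting 150 leaves about 127, or 63 to 64 per group. If all drop-outs are lost to the efficacy analysis, two-sided power for 2.9 points falls from about 63% to 59% (one-sided, about 74% to 71%).

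The arithmetic rests only on the stated 70 per group and 15%. The power figures also assume the stated SD, a simple two-group t-test and equal loss in both arms. The error adds to the understated base number and works in the same direction, so 165 must not be read as enough for 90% power. A sample size statement that its own inputs contradict needs correcting.

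**What to change.** In Sample size calculation, delete the claim that 148 secures the required number. Replace it with a statement that 150 randomised with 15% loss gives about 127 evaluable women (63 to 64 per group), followed by power and detectable difference at that number: about 59% two-sided or 71% one-sided for 2.9 points, and 90% power only for differences of about 4.3 or 3.8 points respectively. Alternatively, state that 150 tolerates a loss of only 6.7% before fewer than 140 remain. That wording leaves 140 standing as the target, so it is acceptable only if the base number is dealt with too.

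Make the change together with the correction of the 70 per group and of the sidedness, and say whether drop-outs count towards the efficacy number, given the intention-to-treat and last-recorded-data rules elsewhere in the article.

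The cost is a corrected sentence or two and a less favourable planning figure. It needs no further enrolment, which matters because the Trial status section expected follow-up to finish by the end of November 2021.

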Descriptive analysis will be used for baseline variables including demographic characteristics, medical history, course of disease, treatment history, combined diseases, concomitant medications, vital signs, laboratory tests for safety assessment, and adverse events. Continuous variables will be expressed by mean ± SD; categorical variables will be shown as counts and percentages. Estimates of the adjusted differences in risks are presented with 95% confidence intervals (CIs) of the difference. The comparability of the characteristics between the BSHX and placebo groups will be assessed by using *t*-test for continuous variables with normal distribution, while the non-parametric Mann-Whitney-Wilcoxon test will be used for the comparison of data with non-normal distribution. Specifically, the paired *t*-test will be used to compare the difference of the outcome between preintervention and postintervention in each group and independent t-test will be used to compare the difference between the two groups. Categorical variables will be compared using *Χ*^2^ statistics, while the Fisher exact test will be used when the theoretical frequency is less than 5 in more than 25% of the cells. In order to control the center and baseline effects, covariance analysis will be applied for the intergroup comparison with continuous variables and Cochran-Man-tel-Haenszel test for categorical variables. The differences of CMS scores, levels of FSH, LH, E2, AMH, the AFC, and ovarian PSV (cm/s) at month 0 and month 3 between the BSHX and placebo groups will be compared using an independent *t*-test. A repeated-measures analysis of variance (ANOVA) test with Bonferroni post hoc test will be used to evaluate the changes in CMS scores, levels of FSH, LH, E2, AMH, the AFC, and ovarian PSV (cm/s) and safety assessment measurements throughout the experiment. In all tests, a value of *p* < 0.05 will be considered statistically significant. All statistical analyses will be performed using SPSS V.20.0.

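### The printed sample-size formula gives 138 women per group (112 with the quoted 1.64), not 70, and 150 women give about 59% to 66% two-sided power, not the stated 90%.

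*Protocol article*

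**What the plan says.** The protocol article's Sample size calculation section bases the trial on the total CMS score. Its effect assumption is: "We assumed that BSHX administration would reduce CMS score by 2.9 points and the SD is 7.42 in the study". It takes a type I error rate of 0.05 and "a power of 90 % (type II error rate of" 0.1), quotes the normal values 1.64 and 1.28, and arrives at about 70 women per group. For losses it allows "the maximum possible drop-out rate of 15%, we need 148 participants in total to achieve the number of people required for the efficacy analysis", and rounds up to 150 recruited. It then says that "the following formula was used to estimate the sample size" and prints n = 2 × [(z(1−α/2) + z(1−β)) × σ/δ]².

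Allocation is 1:1 (Randomization and blinding). The Statistical analysis section sets p < 0.05 for all tests and mentions no one-sided test. It names an independent t-test for the CMS comparison between groups at months 0 and 3, and elsewhere plans covariance analysis to control for centre and baseline.

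**The concern.** The inputs, the formula and the result stand in one paragraph and do not agree. The value 1.64 belongs to a one-sided 5% test, while the formula's z(1−α/2) is 1.96 at α = 0.05. Whichever is used, the formula does not return 70 per group. The step from 140 to 148 does not correspond to 15% loss either.

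What is at stake is how the primary result will be read. A non-significant result in a trial that claims 90% power is taken as fair evidence against the assumed effect. If the real chance of missing that effect is 34% to 41% (two-sided, depending on how many women are analysed), the same result says much less.

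The definition of the effect adds to the doubt. The section gives the aim as a comparison of the two groups before and after treatment, but words the 2.9 points as what BSHX would achieve and states no placebo change.

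**Working it through.** **Inputs** (Sample size calculation section): δ = 2.9, σ = 7.42, α = 0.05, power 90%, z(1−β) = 1.28, drop-out 15%, 150 recruited. Allocation is 1:1.

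**1. The plan's own figure.** (σ/δ)² = (7.42/2.9)² = 6.5465.

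| Critical value | (z + 1.28)² | n per group, formula as printed | Same without the factor 2 |
|---|---|---|---|
| 1.96 (printed formula) | 10.4976 | 2 × 10.4976 × 6.5465 = 137.4, so 138 | 68.7 |
| 1.64 (quoted in text) | 8.5264 | 2 × 8.5264 × 6.5465 = 111.6, so 112 | 55.8 |

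The stated 70 is not reproduced. Only the 1.96 version without the leading 2 comes near it, so 1.64 appears not to have produced the 70.

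**2. Drop-out.** 140/0.85 = 164.7, so 165. Even the common shortcut 140 × 1.15 gives 161. The stated 148 leaves 148 × 0.85 = 125.8 women after 15% loss. It keeps 140 only if the loss is 1 − 140/148 = 5.4%. The 150 recruited leave 150 × 0.85 = 127.5, about 64 per arm.

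**3. Power of the planned trial** (two-sample t-test, δ/σ = 2.9/7.42 = 0.391):

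| Analysed per arm | Two-sided 5% | One-sided 5% |
|---|---|---|
| 64 (15% lost) | 59% | 71% |
| 70 | 63% | 74% |
| 75 (all analysed) | 66% | 77% |

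**4. Difference detectable with 90% power**, two-sided t-test: about 4.3 points at 64 per arm and 4.0 at 75. For scale only, 90% power for 2.9 points would need 2 × 138 = 276 analysed, and 276/0.85 = 325 recruited.

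**5. What baseline adjustment could recover.** Let r be the correlation between baseline and month-3 CMS.

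- If 7.42 is the SD of a single score, covariance analysis multiplies the variance by 1 − r².
- If 7.42 is the SD of a change, the change variance is 2(1 − r) times the score variance, so the factor is (1 − r²)/[2(1 − r)] = (1 + r)/2.

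Two-sided power for assumed values of r:

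| r | Per arm | 7.42 a score SD | 7.42 a change SD |
|---|---|---|---|
| 0.5 | 64 | 72% | 72% |
| 0.7 | 64 | 87% | 66% |
| 0.7 | 75 | 91% | 73% |

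The article gives no r and does not say which SD 7.42 is.

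**The case against.** **Power after losses.** The strongest objection is to reading 59% as the power of 150 women. It is the power after the full 15% is lost, which the article calls a maximum. The section on removal and dropout says that a dropout's last recorded data are analysed, and the Statistical analysis section makes intention-to-treat the main analysis. On those rules up to 75 per arm contribute and power is 66%. This stands, so the result must be given as a range with its conditions. It does not rescue 90%.

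**Covariance analysis.** It is already planned and would raise power. That is true, and with r = 0.7, a score SD and all 75 per arm analysed, power would pass 90%. But the printed formula contains no correlation, none is stated, and the test named for the month-3 CMS comparison is the unadjusted t-test. If 7.42 is a change SD, most of the gain disappears.

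**A single-arm calculation.** A reader might infer that the 70 came from a before-after calculation in the BSHX arm, since a two-sided paired t-test would need 70.7. The article does not support this. It states a comparison between groups, prints a two-group formula and gives equal sizes for two groups. Reading the per-group 138 as the total and halving it to 69 fits as well. The cause cannot be settled.

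**A placebo response.** A reader might also suppose that placebo improves and power is lower still. That rests on reading 2.9 as a within-arm fall and on a placebo change that the article does not give. As speculation only: placebo falls of 0, 0.5, 1.0 and 1.5 points would give 59%, 44%, 30% and 19% at 64 per arm. No conclusion here depends on these.

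**Conclusion.** The point holds as an error of arithmetic and consistency in the basis for the trial's size. The stated inputs require 138 per group (112 on the quoted one-sided value), about 2.0 (1.6) times the stated 70. The allowance for 15% drop-out should give 165, not 148.

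For the assumed 2.9 points with SD 7.42, 150 women give 59% to 66% two-sided power, according to how many are analysed, and 71% to 77% one-sided. The 90% claim fails on each of these. It could be met only through a baseline correlation that the article does not state.

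The figures assume that 2.9 is a between-group difference and that 7.42 is the SD of the quantity compared by the t-test. The wording makes neither certain, and that ambiguity is part of the point. This should be corrected before the results are interpreted.

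**What to change.** 1. State one alpha, two-sided 0.05 as in the printed formula, and delete 1.64.
2. Define 2.9 as the BSHX-minus-placebo difference, or restate it, and say whether 7.42 is the SD of a score or of a change.
3. Correct the drop-out arithmetic.
4. Replace the 90% claim with the power that 150 women give (about 59% to 66% two-sided, with the numbers analysed), or with the difference detectable at 90% power (about 4.3 points at 64 per arm, 4.0 at 75).
5. Before unblinding, name the covariance analysis already in the Statistical analysis section, adjusted for baseline CMS and centre, as the primary between-group test in place of the unadjusted t-test. State its gain only with the assumed correlation and type of SD.

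Items 1 to 4 cost rewording and a less favourable stated power, with no extra patients. Item 5 changes the primary test, so it needs a dated amendment. Recruitment began in February 2020 and follow-up was due to end in November 2021, so item 5 is defensible only if the blind is still intact when it is fixed. Otherwise the adjusted analysis should be labelled as chosen after unblinding.
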